#### Adherence

In order to assess whether changes in SBHC participants’ level of psychological distress are associated with counsellors’ adherence to SBHC competences, we will obtain independent adherence ratings via the aforementioned method, and use these to assess the relationship between adherence and outcome.

#### Pastoral care log

A member of the pastoral care team records any instances of care as usual delivered to participants in the trial in a Pastoral Care Log throughout the trial. This data will be used to assess the level and nature of pastoral care delivery across included schools, and any mediating impact on outcomes.

#### Adverse event monitoring

Individuals in contact with trial participants (including pastoral care staff, assessors, counsellors (and their supervisors) testers and qualitative interviewers) are required to use an Adverse Events (AEs) Reporting Log to record the occurrence of any AE in a trial participant throughout the trial (see below).

### Sample size

Sample size was calculated to take into account clustering and participants lost to follow-up. Firstly, without either clustering or participants lost to follow-up, for 90% power to detect a standardised mean difference (SMD) of 0.5, 86 participants would be required per arm (172 in total). The effect size was determined by pooling findings on the primary outcome from four previous studies and making a conservative estimate [24, 31–33]. Intra-class correlation coefficient (ICC) for counsellors was estimated from prior data as 0.05 [24, 31–33]. On average, we estimated that nine young people could be seen per counsellor (4.5 on average per assessment phase); if there is 20% loss to follow-up, this leaves a mean of 7.2. The ICC and average number of young people together leads to a design effect of 1.31, which, when multiplied by the pre-cluster sample size, gives 1.31 × 86 = 113 (rounded up). Hence, after loss to follow-up has taken place, 113/7.2 = 16 (rounded up) practitioners are required per arm. Add 1 [57] to give 17 counsellors. To find the number before loss to follow-up, we calculated 17 × 9 = 153 participants required per arm and 153 × 2 = 306 in total.

### Data quality and management

#### Training of assessors and testers

All assessors and testers are provided with comprehensive training in the study and the purposes and principles of the research meetings, including key study documentation, before conducting any research meetings with participants. Assessors have a diploma in counselling or psychotherapy (or are currently enrolled in a diploma-level training in counselling or psychotherapy or equivalent) and have experience of working with young people (aged 13 years onwards) and using outcomes measures in clinical assessment. Study-specific assessment guidelines have been developed for the trial and are used in assessment training, and each assessment meeting. These provide guidance on administration of all measures at baseline, and evaluating eligibility of each potential participant. This includes risk assessment and management, and assessment of Gillick competency. Testers have a completed (or are currently studying for) a postgraduate course in psychology, counselling, or a related discipline. The well-being of the young person is of paramount importance and testers are trained to sensitively work with significant levels of distress if it arises during a research meeting. Study-specific tester guidelines have been developed for the trial and are used in tester training, and each testing meeting. These provide guidance on administration of all measures at 6 weeks/mid-point, 12 weeks/endpoint and 24 weeks/follow-up. The assessor and tester guidelines contain a glossary of words/phrases used in the outcome measures that participants may struggle to comprehend. Assessors and testers are trained to use this glossary, as needed, to ensure that the process of administrating measures is as standardised as possible.

#### Data entry and storage

All personal data (e.g. signed consent forms, participants’ date of birth) are stored in a locked cabinet. Anonymised quantitative measures and educational attainment/engagement data are collected on hard copies and stored in a separate locked filing cabinet from personal data. Partially anonymised data (e.g. audio-recordings of sessions) are kept temporarily on password-protected, encrypted, recording Android devices, and transferred to encrypted, password-protected servers at the University of Roehampton. Anonymised quantitative measures are password protected and submitted as electronic copies to MAHSC-CTU. Scanned copies of CRFs transferred to the CTU are stored securely within MAHSC-CTU offices and in accordance with the Data Protection Act [58]. The trial adheres to the Economic and Social Research Council’s (ESRC) Research Data Policy and the Centre for Research in Social and Psychological Transformation (CREST, Department of Psychology at the University of Roehampton), Data Storage and Protection Procedures.

Data will be entered by MAHCS-CTU staff onto DBS: a restricted-access and bespoke-validated clinical trial database managed by MAHSC-CTU. Data validation is run on the data entered and data queries and corrections are sent to the researchers to clarify and correct anomalous data. Prior to the end of the study, quality control checks will be conducted, prior to the database being finalised.

#### Trial monitoring

Trial monitoring will be performed by the University of Roehampton which will conduct regular audits and site visits to schools; and MAHSC-CTU which will conduct a mixture of remote monitoring of essential documentation and on-site monitoring of source data. The site checks will aim to verify that the rights and well-being of participants are protected; verify accuracy, completion and validity of reported trial data from the source documents; and evaluate the conduct of the trial within the school with regard to compliance with the approved protocols.

### Confidentiality

Names of participants on the consent forms (personal data) are stored separately from anonymised data in locked filing cabinets and only accessible by named personnel. A separate code (‘pre-randomisation code’) links names to Participant ID numbers used in data files, which are password protected and only accessible by named personnel.

### Statistical methods

Statistical analysis will be carried out by the ETHOS principal statistician and economist according to a statistical analysis plan agreed in advance. The principal statistician will be blind to the randomisation, with the exception of analysis of the WAI-S which is only completed by participants in the SBHC group. Allocation for all other measures will be coded as a non-identifiable variable in the clinical effectiveness analysis to minimise potential bias. The principal economist cannot be blind to allocation due to the nature of the data being analysed (e.g. number of counselling sessions attended).

#### Analysis of clinical effectiveness

The primary analysis will be based on the intention-to-treat principle. Per-protocol analysis will also be conducted. Baseline characteristics will be described by group and pooled using mean, standard deviation (SD), minimum, maximum, median, and interquartile range. Categorical variables will be described by frequency. Analyses will be performed using linear mixed-effects models (LMMs) including data from all randomised participants by intention to treat. All variables used for stratification/minimisation will be included as covariates (random intercept for school and practitioner; fixed effect for other baseline characteristics). Differences between SBHC and PCAU will be summarised by 95% CIs of the difference between groups, estimated by the LMMs. Given the likely non-linear patterns of change and measures taken at discrete time points, analyses will be conducted at each time point, adjusted by baseline scores. Standardised mean differences will be calculated using the LMM-estimated mean differences between groups at each time point after baseline, divided by the baseline SD. Sensitivity analyses will be conducted to test for any moderating effects of support provided to participants to complete measures. Participants with and without missing data will be compared using baseline characteristics, including intervention allocation, to test for patterns of missing values and systematic biases. Multivariate imputation by chained equations will be used to compute questionnaire scores for participants with missing item responses.

Secondary analysis will include modelling of the extent to which the relationship between intervention allocation and outcome is mediated by the BLRI variables, and testing for differences in the frequency of AEs by allocation. Data will also be analysed within the treatment group to determine whether outcome is predicted by mid-point therapeutic alliance, while adjusting for all baseline variables.

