#### Delivery of SBHC

SBHC is delivered over ten school weeks, in up to ten weekly, face-to-face sessions of between 45 and 60 min each (depending the length of a school period) on an individual basis. All participants allocated to the SBHC group are able to continue accessing their school’s pastoral care services as needed. There are no modifications to the trial intervention, such as an extension to the agreed number of sessions. Participants may choose to end their counselling sessions before they have completed ten sessions in total.

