### Control group: Pastoral Care as Usual (PCAU)

‘Pastoral care’ in UK schools is a generic, umbrella term used to describe targeted services offered by the school to support the well-being of pupils on roll. Such services vary across schools and while there is no one approach, the existence of such services within schools is a standard practice and seen as inextricably linked to teaching, learning, and the curriculum. For many UK schools, in particular those with limited financial resources, pastoral care is the only provision on offer to accommodate pupils’ well-being needs as targeted interventions, such as counselling, are seen as too costly. Despite the differences in pastoral care services across UK schools, there are also some similarities in the models and approaches employed. For example, form tutors may be tasked with monitoring any emotional difficulties as they arise for pupils in their form group, policies and guidance will be in place relating to bullying and behaviour, schools will have established links to local external services or agencies, for example Child and Adolescent Mental Health Services (CAMHS). School pastoral care services in the UK do not routinely offer counselling, and differ from humanistic counselling in several ways: (1) pastoral care is offered by any member of staff, whatever their qualifications, (2) pastoral care is advice-giving and directive, (3) pastoral care does not involve a collaborative contract, with an agreement on boundaries, confidentiality, or therapeutic goals, (4) pastoral care is most often provided ‘ad hoc’, and is not time limited while the pupil is on roll.

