PCAU within the current study, therefore, consists of the included schools’ pre-existing, ‘as usual’ systems for supporting the emotional health and well-being of young people within their particular school, which may involve a personal tutor, or a school inclusion lead meeting regularly with the young person to speak about their difficulties. PCAU does not consist of humanistic counselling, but additional school and non-school-based interventions for young people may be provided, such as a short placement in a learning support unit, some one-to-one support or group work from a school nurse, learning mentor, educational psychologist or behaviour support team, and interagency meetings (for example, the creation of a Common Assessment Framework). The intensity and length of support will depend upon the specific needs of each young person. The number of interventions and the specific form of support is recorded by the pastoral care team in a pastoral care log (see below). Participants randomly assigned to the PCAU condition will be offered the opportunity to access SBHC 6 to 9 months after their assessment.

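### If the planned per-protocol set is defined by sessions attended, it would drop self-selected pupils from SBHC only; a CACE analysis should be the main supportive estimate of the effect of receiving counselling

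*Protocol article*

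**What the plan says.** Under Analysis of clinical effectiveness the protocol article states: "The primary analysis will be based on the intention-to-treat principle". It then adds: "Per-protocol analysis will also be conducted". It does not say who belongs to the per-protocol set. Statistical methods says that the analysis will be done "according to a statistical analysis plan agreed in advance"; that plan is not shown.

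The two arms differ in whether there is anything to complete:

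- **SBHC** (Delivery of SBHC) is given "in up to ten weekly, face-to-face sessions of between 45 and 60 min each". No minimum is stated, and "Participants may choose to end their counselling sessions before they have completed ten sessions in total".
- **PCAU** (Control group) is described thus: "pastoral care is most often provided ‘ad hoc’, and is not time limited while the pupil is on roll". For the trial's own control arm, "The intensity and length of support will depend upon the specific needs of each young person".

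PCAU pupils are offered SBHC 6 to 9 months after assessment, which is after the last outcome at 24 weeks. No CACE or other instrumental-variable analysis is mentioned.

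**The concern.** The most natural reading of per-protocol in a counselling trial is attendance at enough sessions. Under that reading, exclusions fall on SBHC, because only SBHC has sessions to count. The PCAU pupils who would have left counselling early, had they been offered it, cannot be identified and stay in the comparison. SBHC pupils who persisted are then compared with all PCAU pupils.

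Leaving is the pupil's own choice and may be related to how the pupil is doing. The article's list of adverse events includes a problem with the counsellor that leads to counselling being discontinued. If leavers have a different prognosis, the comparison can show an effect where there is none, or hide part of a real one. A reader who sees this estimate beside the intention-to-treat result may take it as the effect of actually receiving counselling.

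**Working it through.** **The plan's own figures.** The article gives no number for the per-protocol analysis, but its sample size supplies the scale. For SMD 0.5 and 90% power (two-sided 5% assumed, as alpha is not stated), the normal formula gives 85 per arm and the t distribution 86, matching the stated 86. The design effect is 1 + (7.2 − 1) × 0.05 = 1.31. Then 1.31 × 86 = 112.7, rounded up to 113; 113/7.2 = 15.7, rounded up to 16; 16 + 1 = 17; 17 × 9 = 153 per arm, 306 in total. All of this reproduces. After 20% loss, 153 × 0.8 = 122 per arm.

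**Assumed inputs.** The article gives no share of early leavers and no prognostic gap. Let p be the share of SBHC pupils excluded, g the amount (in SD, after baseline adjustment) by which leavers' distress would be higher whatever their arm, τ the effect in completers, and f the fraction of τ that leavers still gain. Effects are reductions in distress.

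**Per-protocol with exclusions in SBHC only.** Let μ be the untreated mean of pupils who would complete. The PCAU mean is μ + p×g and the SBHC completers' mean is μ − τ. The difference is τ + p×g, so the bias is p×g.

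| p | g | Bias (SD) | Share of 0.5 |
|---|---|---|---|
| 0.1 | 0.3 | 0.03 | 6% |
| 0.2 | 0.4 | 0.08 | 16% |
| 0.3 | 0.4 | 0.12 | 24% |
| 0.3 | 0.6 | 0.18 | 36% |
| 0.4 | 0.5 | 0.20 | 40% |

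A negative g reverses the sign, and g = 0 gives no bias.

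**When counselling has no effect.** In 4,000 simulated trials with 122 per arm, unit SD, no clustering and no baseline covariate, the nominal 5% per-protocol test rejected in 10% of trials (p = 0.2, g = 0.4), 13% (0.3, 0.4) and 25% (0.3, 0.6). A normal approximation agrees. For the first case the SE is √(1/122 + 1/98) = 0.136, and 0.08/0.136 = 0.59, giving about 9%. The other two cases, with 85 SBHC pupils left, give about 14% and 25%. The CACE estimate averaged within 0.002 SD of zero in all three.

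**CACE.** The intention-to-treat effect is (1 − p)τ + p×f×τ. Dividing by 1 − p gives τ + [p/(1 − p)]×f×τ. The bias is therefore [p/(1 − p)]×f×τ. It does not depend on g, and it vanishes when τ = 0 or f = 0. With τ = 0.5 and f = 0.5 it is 0.03, 0.06, 0.11 and 0.17 SD at p = 0.1, 0.2, 0.3 and 0.4.

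**Side by side, true effect 0.5 in completers, p = 0.2** (large-sample simulation):

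| g | f | ITT | Per-protocol | CACE |
|---|---|---|---|---|
| 0.5 | 0 | 0.40 | 0.60 | 0.50 |
| 0 | 0.5 | 0.45 | 0.50 | 0.56 |
| −0.5 | 0.5 | 0.45 | 0.40 | 0.57 |

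**The case against.** Three stronger conclusions are tempting, and the document supports none of them.

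1. *A reader might infer that the per-protocol set can exclude only SBHC pupils who stopped.* The article does not define the set, and a protocol commonly leaves that to the analysis plan. Early stopping is permitted, so leavers need not be excluded at all. A set could also remove pupils in either arm for eligibility breaches or off-schedule assessments, or PCAU pupils who obtained counselling early. The concern is therefore conditional on an attendance-based definition.

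2. *A reader might infer that the estimate is certainly biased.* It is at risk of bias, in an unknown direction. The article adjusts its analyses for baseline scores; if the per-protocol model does the same, g is only the gap left after adjustment, and nothing in the document fixes its size.

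3. *A reader might infer that CACE answers the same question without bias.* It estimates the effect in compliers, and a threshold version requires that pupils below the threshold gain nothing. The article's pooled pilot data cast doubt on that for a high threshold: g was 0.47 at 6 weeks against 0.72 at 12 weeks, a ratio of 65%. If leavers gained 65% of a 0.5 effect, the CACE bias would be 0.25 × 0.65 × 0.5 = 0.08 SD at p = 0.2 and 0.43 × 0.65 × 0.5 = 0.14 SD at p = 0.3. That is similar to the per-protocol bias at g = 0.4 (0.08 and 0.12).

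Intention to treat is already primary, and nothing in the article says that the per-protocol result will be presented as the effect of receiving counselling. These points limit the finding but do not remove it. PCAU still has no course to complete, so attendance cannot be defined in both arms. The two biases also differ in kind: CACE bias scales with a real effect and disappears without one, whereas per-protocol bias can produce an effect from nothing.

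**Conclusion.** The point holds in conditional form. The article commits to a per-protocol analysis, and the design means that an attendance-based version would select pupils in one arm after randomisation. For p from 0.1 to 0.4 and g from 0.3 to 0.5 in either direction, the bias is 0.03 to 0.20 SD against a target of 0.5. It is zero if leavers do not differ in prognosis. All of these inputs are assumed.

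The effect on the trial's conclusions is limited because the primary analysis is unaffected. This is an inexpensive improvement to a supportive analysis, not an error in the main one. The design suits CACE: schools with existing or planned counselling were not included, and SBHC reaches PCAU pupils only after the last outcome, so non-compliance is essentially one-sided.

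**What to change.** - Keep intention to treat as primary.
- Make a CACE analysis of YP-CORE the main supportive estimate of the effect of receiving counselling. Use randomisation as the instrument, either for a pre-stated low session threshold or for the number of sessions attended, with the same school and baseline adjustment as the primary model.
- If an attendance-based per-protocol result is still reported, label it as a non-randomised comparison and place it below the CACE result.
- State the CACE assumptions: the estimand is the effect in compliers; the threshold version relies on the exclusion restriction and overstates a real effect if pupils below the threshold also benefit; the session-count version relies on a linear dose effect.

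**Cost.** One additional model and no new data: Statistical methods already names the number of counselling sessions attended among the data for the economic analysis. The interval is wider, by roughly 1/(1 − p) relative to intention to treat, or 1/0.8 = 1.25 times at p = 0.2. Session counts reveal allocation, and the principal statistician is to be blind, so the model should be run after the blinded primary analysis or by someone else. An attendance-based per-protocol analysis would raise the same issue.

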#### Primary outcomes

##### Young Person’s Clinical Outcomes in Routine Evaluation (YP-CORE)

The primary outcome measure is the YP-CORE [34], a 10-item, self-report, 5-point Likert-type scale measuring psychological distress. Participants are asked to rate how they have been feeling over the last week (prior to completing the questionnaire) in relation to 10 items. Individual item scores range from 0 (‘not at all’) to 4 (‘most or all of the time’) with a total YP-CORE score ranging from 0 to 40. The YP-CORE was chosen because it is a clinically relevant measure to assess changes in psychological distress in the age group being studied in the current trial, and because it has demonstrated internal reliability (*α* = 0.80) and test-retest reliability across 1 week (*r* = 76, 95% CI 0.65 to 0.86) [34]. The YP-CORE is administered at assessment/baseline, mid-point/6 weeks, endpoint/12 weeks, and follow-up/24 weeks.

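### As worded, the YP-CORE analysis at each time point leaves out anyone who missed that visit, although the model is said to include all randomised participants

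*Protocol article*

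**What the plan says.** All the modelling statements are in the protocol article, under Analysis of clinical effectiveness.

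- Population: "Analyses will be performed using linear mixed-effects models (LMMs) including data from all randomised participants by intention to treat".
- Time: because change is expected to be non-linear and visits are discrete, "analyses will be conducted at each time point, adjusted by baseline scores".
- Stratification variables enter the model as "random intercept for school and practitioner; fixed effect for other baseline characteristics". No participant-level effect and no covariance across visits is mentioned.
- Imputation: "Multivariate imputation by chained equations will be used to compute questionnaire scores for participants with missing item responses".
- The only other missing-data step is descriptive: "Participants with and without missing data will be compared using baseline characteristics, including intervention allocation".

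The YP-CORE section gives three post-baseline visits: "The YP-CORE is administered at assessment/baseline, mid-point/6 weeks, endpoint/12 weeks, and follow-up/24 weeks". The Sample size section plans for attrition without tying it to a visit: "if there is 20% loss to follow-up, this leaves a mean of 7.2". The Pilot studies section reports that between 76.2% and 100% of pupils completed to endpoint.

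**The concern.** A baseline-adjusted model for one visit has one outcome row per participant. Someone who missed the visit has no row, and with no participant-level term the model cannot draw on that person's other post-baseline scores. That is an available-case analysis, and it does not match the statement about "including data from all randomised participants by intention to treat".

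The imputation sentence, read plainly, deals with part-completed forms and not with missed visits. The baseline comparison of those with and without missing data cannot detect loss that depends on the 6-week score.

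The reason given does not require this approach. A single model with visit as a categorical factor makes no assumption about the shape of change and still gives a difference at every visit.

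At stake are the 12- and 24-week estimates, where the discarded scores exist. At 6 weeks the only earlier score is baseline, which is already in the model. If staying in the study depends on the 6-week score differently in the two arms, the per-visit estimate is biased and a joint model can correct it.

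**Working it through.** **1. The plan's own sample size.** Inputs from Sample size: standardised difference 0.5, 90% power, ICC 0.05, nine young people per counsellor, 20% loss. Alpha is not stated there; two-sided 0.05 is assumed.

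- Per arm before clustering: the t-based solution is 85.03, rounded up to 86, as stated.
- Mean cluster after loss: 9 × 0.8 = 7.2.
- Design effect: 1 + (7.2 − 1) × 0.05 = 1.31.
- 1.31 × 86 = 112.66, so 113; 113/7.2 = 15.69, so 16; plus 1 gives 17.
- 17 × 9 = 153 per arm; × 2 = 306. This reproduces the stated figure.

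**2. How many a per-visit model leaves out.**

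- Planned loss: 306 × 0.20 = 61.2, about 61. That leaves 244.8, or 122.4 per arm.
- Pilot range: loss of 0% to 100 − 76.2 = 23.8%; 306 × 0.238 = 72.8. So 0 to about 73.

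**3. Power.** Effective number per arm is 122.4/1.31 = 93.4. Power for 0.5 SD is Φ(0.5 × √(93.4/2) − 1.96) = 92.8%. Power is not the problem.

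**4. Bias.** The documents give neither the correlations nor the loss mechanism, so these are assumptions. The simulations used 153 per arm, no clustering in the main check, and about 20% loss, all after week 6 unless noted. They compared a 12-week baseline-adjusted model on observed cases with a likelihood estimate that also uses the 6-week score. The true difference is 0.50 SD in favour of SBHC.

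| Assumed loss | Correlations | Per-visit | Joint |
|---|---|---|---|
| Random | 0.45–0.65 | 0.50 | 0.50 |
| Depends on 6-week score, same in both arms | 0.45–0.65 | 0.49 | 0.50 |
| Only worsening PCAU pupils lost, log-odds 0.8 per SD | 0.45–0.65 | 0.44 | 0.50 |
| Opposite by arm, log-odds 0.4 per SD | 0.45–0.65 | 0.43 | 0.50 |
| Opposite by arm, log-odds 0.8 per SD | 0.45–0.65 | 0.37–0.38 | 0.50 |
| Opposite by arm, log-odds 1.0 per SD | 0.5 with baseline, 0.7 between weeks 6 and 12 | 0.34 or 0.66, by direction | 0.50 |

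With half the loss occurring at random before week 6, the opposite-by-arm per-visit estimate moves to 0.43 (log-odds 0.8) or 0.46 (log-odds 0.4).

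Under random loss the standard errors are 0.115 against 0.111 in one set of runs and 0.113 against 0.109 in the other. Both ratios are about 1.04.

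Coverage of the nominal 95% interval is about 79% at log-odds 0.8 and about 70% at log-odds 1.0, both with opposite mechanisms.

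**5. Analytic check of the last row.** Bias is the slope of week 12 on week 6 given baseline, times the between-arm shift in completers' baseline-adjusted 6-week score.

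- Slope: (0.7 − 0.5 × 0.5)/(1 − 0.5²) = 0.45/0.75 = 0.60.
- Shift per arm: log-odds × mean of p(1 − p) × (1 − 0.5²)/0.8, where p is the probability of loss. With p averaging 0.2, the mean of p(1 − p) is 0.139 by numerical integration. So 1.0 × 0.139 × 0.75/0.8 = 0.130.
- Opposite signs in the two arms double it: 0.60 × 2 × 0.130 = 0.156, in line with the simulated 0.16.

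**The case against.** The article never uses the word separate. Its next sentence, on standardised differences, speaks of model-estimated group differences at each visit after baseline, which one model with categorical visit would also supply. The bracket naming school and practitioner describes how stratification variables enter; it does not claim to list every random effect. Covariance structure is ordinary content for a statistical analysis plan, and that plan is not at hand. A missed visit could also be regarded as a form with every item missing, which would bring it under the imputation sentence.

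This stands as a limit on certainty. A reader might infer that the protocol expressly prescribes three independent models; it does not. Analysis by visit is nevertheless the natural reading, because non-linearity is given as its reason and nothing in the text links one visit to another.

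The size of the bias is also open to challenge. The large figures need strong loss, opposite by arm, after week 6, and the documents do not show that. Several design features work against it: research meetings sit in the school timetable and pastoral staff follow up absentees, eligibility asks for 85% school attendance, and pupils planning to leave the school are excluded. Ending counselling early is not the same as missing a research meeting. Baseline-adjusted analysis by visit is a recognised method and is valid if loss is ignorable given arm and baseline. All of that stands, and it is why the size is given as a range that includes no bias.

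**Conclusion.** The point holds as a conflict between the stated population and the analysis as naturally read, with a better method available from data already collected. About 61 of 306 participants would be left out at the planned loss (0 to about 73 on pilot rates).

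The consequence depends on why people are lost. Bias is nil under random loss and about 0.01 SD under the same mechanism in both arms. It reaches roughly 0.12 to 0.16 SD, in either direction, under strong and opposite mechanisms, and is smaller if part of the loss comes before week 6. These figures rest on assumed correlations and mechanisms.

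Three stronger conclusions are not supported:

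- That the trial is underpowered: the 306 already allows for 20% loss.
- That the treatment effect will be understated: the direction depends on which participants leave each arm.
- That the 12-week result in particular is compromised as the primary one: the protocol names no primary visit, and endpoint is used there as a visit label.

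Nor does a joint model remove all bias. It does so only if loss is missing at random given the observed scores, and it recovers little for participants with no post-baseline score.

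**What to change.** Specify one linear mixed model for YP-CORE at 6, 12 and 24 weeks, with visit as a categorical factor, arm-by-visit and baseline score-by-visit terms, an unstructured within-participant covariance, and the school and practitioner terms already planned. Read the contrast at each visit from this model, without labelling any visit primary on the strength of this change. Keep the item-level imputation for part-completed questionnaires.

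Alternatively, keep the analysis by visit and state that the chained-equations imputation also covers whole missed questionnaires and uses earlier YP-CORE scores.

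In either case, describe the analysed population accurately: under the joint model, all randomised participants with at least one post-baseline score, unless wholly missing participants are also imputed. State the missing-at-random assumption. If the statistical analysis plan already specifies one of these approaches, only the published wording needs to be aligned with it.

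The cost is revised wording and slightly more modelling work. No new data are needed and the sample size stays at 306. The downside is that validity then rests on loss being missing at random given the observed scores.
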